## Abstract

**Background:**

Major Depressive Disorder (MDD) is highly prevalent and was associated with greater morbidity, mortality (including suicide), and healthcare costs. By 2030, MDD will become the leading cause of disability in high-income countries. Notably, among patients with a previous experience of a major depressive episode, it was indeed estimated that up to 85 % of those patients will suffer from relapse. Two main factors were associated with a significantly higher risk of relapse: poor medication adherence and low self-efficacy in disease management. Interestingly, these issues could become the targets of psychoeducational programs for chronic diseases. Indded psychoeducational program for depression are recommended in international guidelines, but have not yet been proposed in France.

**Methods/Design:**

We propose to evaluate the first French psychoeducational program for depression “ENVIE” in a multicenter randomized controlled trial. The group intervention will include 9 weekly sessions. Its aim is to educate patients on the latest knowledge on depression and effective treatments through didactic and interactive sessions. Patients will experiment the latest innovating psychological skills (from acceptance and commitment therapy) to cope with depressive symptoms and maintain motivation in behavioral activation. In total, 332 unipolar non-chronic (<2 years) outpatients with moderate to severe depression, without psychotic features, will be randomly allocated to the add-on ENVIE program (*N* = 166) or to a waiting list (*N* = 166). The follow-up will last 15 months and include 5 assessment visits.

The primary endpoint will be the remission rate of the index episode at 15 months post-inclusion, defined by a Montgomery and Asberg Depression Rating Scale (MADRS) score ≤ 12 over an 8-week period, and without relapse during follow-up. We will also assess the response rate and relapse at 15 months post-inclusion, hospitalization rate and adherence to treatment during the follow-up period, quality of life and global functioning upon inclusion and at 9 and 15 months post inclusion.

**Discussion:**

If the proposed trial shows the effectiveness of the intervention, but also an increased remission rate in depressed outpatients at 15-months post-inclusion, in addition to improved treatment adherence in patients, it will further promotes arguments in favor of a wide dissemination of psychoeducational programs for depression.

**Trial registration:**

This trial is registered under number 2015-A00249-40 (PURE clinical trial: NCT02501226) (June 30th, 2015).

## Background

MDD is associated with a considerable burden on individuals and societies and a lifetime prevalence of 12 % in men and 26 % in women [1], MDD ranks as the fourth disorder having the highest disease burden, accounting for 40.5 % of DALYs caused by mental disorders [2]. MDD will be the leading cause of disability in high-income countries by 2030. MDD has been associated with greater morbidity, mortality (including suicide), healthcare utilization and costs [3]. Economic costs of depression have doubled in the past ten years, mainly due to an increase in indirect costs from loss of productivity [4, 5]. There is a clear need to improve MDD management without increasing public mental health costs.

Although clinical improvement is often achieved in 60–70 % of depressed patients treated with antidepressants, only about 35 % will reach remission [6, 7]. In addition to antidepressants, complementary therapeutic strategies are needed. Furthermore, among patients who experienced one major depressive episode, it is estimated that up to 85 % of them will relapse [1]. Moreover, patients who experienced two episodes, have a 70–90 % risk of having a third episode [1] The probability of subsequent episodes increases with the number of previous episodes, with a shorter interval between recurrences [8]. These data highlight the need to improve preventive actions to limit depression recurrence. Two main factors have been associated with a significantly higher risk of recurrence: poor medication adherence and low self-efficacy to manage one’s illness (i.e. the patient's confidence in his or her ability to engage in behaviors to manage and prevent further recurrences) [1]. Interestingly, these two factors are targets of psychoeducational programs for chronic diseases. Indeed, these types of programs are designed to educate patients on topics that are essential and can empower them to become active in their recovery process through knowledge and information. Benefits of empowerment include improved self-image, self-efficacy, as well as increased ability to cope with daily life and a higher likelihood of reaching treatment goals [9].

Even if most research on psychoeducation for patients with mood disorders was conducted in bipolar disorder [10], international clinical practice guidelines recently recommended psychoeducational interventions in MDD [11–13]*.* Psychoeducation in MDD was shown to: 1) reduce depressive symptoms [5, 14–29], 2) reduce the risk of relapse or recurrence [26, 30–33], 3) improve treatment adherence [17, 18, 34], 4) increase quality of life [29] and global functionning [25, 35]. In these studies, the program “Coping with depression” (CWD) was the most used. CWD is a cognitive behavioral psychoeducative intervention based on the theory of depression and social learning [36], which aims at improving self-esteem, social skills, and management of depressive thoughts (skills in restructuring negative cognition). A recent meta-analysis [26] that included 25 randomized controlled trials showed that CWD was effective in reducing depressive symptoms (overall mean effect size of 0.28 (95 % CI:0.18–0.38)), and in preventing relapses (overall mean effect size of 0.62 (95 % CI: 0.43–0.91)). But CWD is complex and requires up to 16 sessions. Thus, other psychoeducational formats have been developed: psychoeducational cognitive workshops [14, 15, 19] and videotaped educational materials [37, 38]. However, most studies had a short-term follow-up limiting the interpretation of the effectiveness of these psychoeducational programs on the long-term management of MDD.

To our knowledge, no psychoeducational program for MDD is available in the French language. Thus, even though international guidelines recommend integrating a psychoeducational program in MDD treatment, none has yet been made available in France. We have developed the first French psychoeducational program for depression called “ENVIE”. This group intervention consists of 9 weekly sessions. It aims at teaching patients the latest knowledge on depression and effective treatments, through didactic and interactive sessions. Patients will experiment the last innovating psychological skills to cope with depressive symptoms and maintain their motivation in behavioral activation [39, 40]. Moreover, the latest innovating psychological skills, which will be taught in the “ENVIE” program, belong to Acceptance and Commitment Therapy (ACT) [41]. Interestingly, ACT has shown equal to superior effectiveness compared to traditional cognitive behavioral therapy on unipolar depression [42–45]. Additionally, the specific impact of ACT skills was recently reported on suicidal risk [46, 47], which was highly associated with depression. Finally, patients will become experts and actors in the management of their disease in order to enhance treatment adherence, since lack of the latter has been strongly associated with an increased risk or relapse.

### Objective and research questions

Primary objective:

The main objective is to compare the effectiveness (rate of remission of index episode at 15 months post inclusion, without relapse during follow-up) of the add-on ENVIE psychoeducational program vs. regular treatment only, in unipolar non-chronic (<2 years) outpatients with moderate to severe depression, without psychotic features.

Secondary objectives:

Comparing add-on psychoeducational program with treatment as usual in regards to:Decrease in depression intensity between inclusion and at 3, 6, 9 and 15 months post inclusion;Response rate 15 months after inclusion;Relapse rate 15 months after inclusion;Hospitalization rate during the follow-up period;Treatment adherence (antidepressants) between inclusion and at 3, 6, 9 and 15 months after inclusion;Changes in quality of life and global functioning between inclusion and at 9 and 15 months after inclusion;Modification of psychotropic treatments between inclusion and at 15 months post inclusion.

## Methods

### Design

We will conduct a two-arm randomized controlled trial, in order to compare the effectiveness of add-on psychoeducational program for unipolar depression vs. treatment as usual in depressed outpatients. This trial will take place in 11 French centers.

Based on medical records, eligible unipolar outpatients suffering from non-chronic (duration of current episode <2 years) major depressive episode (DSM-IV criteria) of moderate to severe intensity (MADRS score >24) will first be screened in each center. During the inclusion visit, participants matching all inclusion criteria and presenting no exclusion criteria will be informed by the investigator and invited to sign a consent form. They will be randomized in one of the two arms: add-on psychoeducational program (interventional group) or waiting list (control group). An independent researcher, not otherwise involved in the study, will perform the allocation. Each patient will be followed during 15 months with 5 visits: at baseline (V1), 3 months (V2), 6 months (V3), 9 months (V4) and 15 months (V5) after baseline. Blinded and trained evaluators will assess patients during the follow-up.

This research, involving human subjects, has been performed in accordance with the Declaration of Helsinki. The study protocol has been approved by an appropriate ethics committee (CPP Sud Méditerranée IV) (covering all 11 participating centres) and is registered under number 2015-A00249-40 (PURE clinical trial: NCT02501226) (June 30th, 2015).

### Sample size

For the control group the full remission rate at 15 months is expected to be 30 % [48]. If, in the experimental group, this rate is 15 % higher, with a power of 0.80 and a two-tailed significance level at 0.05, the sample size ends up to 166 patients per group. Because loss to follow-up will be considered as “not in remission”, no adjusted sample size for taking dropouts into account has to be established. Thus, a total number of 332 subjects will be enrolled in the study. Each center will recruit between 20 and 40 patients: one to 2 psychoeducational groups of 8–10 patients and 10–20 patients in the control group.

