#### Eligibility assessment and randomization

People who apply for participation in the study will receive an information letter with comprehensive details on study procedures. Signed written informed consent will be obtained from all participants. They will be informed that they can withdraw from the intervention and/or study at any time without any negative consequences.

The first visit will consist in evaluating the following data:○ Sociodemographic characteristics: age, gender, nationality, marital status, educational level, employment status;○ Psychopathology using the Mini-International Neuropsychiatric Interview (M.I.N.I.) [50];○ Number of previous depressive episodes, date of onset of the current episode;○ Depression intensity using the Montgomery Asberg Depression Scale (MADRS) and Beck Depression Inventory (BDI);○ Global functioning using the Functioning Assessment Short Test (FAST);○ Quality of life using the World Health Organization Quality Of Life measure-26 (WHOQOL-26) scale;○ History of psychotropic treatment (name, dose);○ Treatment adherence using the Medication Adherence Rating Scale (MARS);○ Lifetime suicidality using the Columbia–Suicide Severity Rating Scale (C-SSRS).

All inclusion and non-inclusion criteria will be checked by the study investigator. Patients will then be informed of their eligibility and randomized with the Capture Software System (Clinsight). Randomization will be performed with a permuted-block 1:1 ratio randomization list with varying block sizes and will be stratified in participating centers. Allocation concealment will be achieved by a centralized randomization procedure via an electronic case-report form.

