## Intervention

### ENVIE: the first French psychoeducational group program

#### Add-on psychoeducational group program

The intervention will consist of 9 weekly, 90-min sessions led by two trained educators (nurse and medical doctor). Each group will consist of 8–10 participants. The ENVIE program will provide participants with the latest medical knowledge on depression and effective treatments in a didactic manner [51–57], as well as the latest innovating psychological skills to cope with depressive symptoms and maintain motivation in behavioral activation [39, 40, 58]. These psychological skills belong to Acceptance and Commitment Therapy [58].

The program includes 9 sessions, each focusing on a specific theme or skill:Presentation of the program and the matrix, and psychotherapeutic tools used during the entire program to motivate patients to behave in a manner that is consistent with what is important in their life [58].Functional analysis of depression using the matrix (patients are taught to understand which symptoms/behaviors are linked to depression, why they feel they are struggling, and what they can do to stop the struggle)Causes leading to depressionConsequences of depression and comorbiditiesNeurobiological bases of depressionSelf-analysis of mood state, recognition of prodromal symptoms of relapseInformation about antidepressants, and evidence-based medical treatments for unipolar depressionLifestyle recommendationsBehavioral activation skills

During sessions, participants will be encouraged to raise questions about anything they want to know about depression. To enhance the active role of patients, each session will be followed with take-home homework.

One or two psychoeducational groups of 8 to 10 patients will be planned in each center.

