#### Primary outcome

The outcome of interest is the probability of remission achievement (rate of remission) of the index episode at 15 months post inclusion. Time to remission is defined as the number of days between the date of inclusion and remission or the last follow-up visit in case of no remission (maximum duration: 15 months). But the exact time of this event will not be known (the event could occur during the interval of two visits), so we will use methods for the analysis of interval-censored data. For calculation, all patient lost to follow-up will be considered as not in remission. A Cox proportional hazard model will be used to assess the impact of the intervention (Effect size). Covariates could be added in the Cox’s proportional hazards regression model if both groups cannot be compared on baseline characteristics alone. The adjusted hazard ratios and their 95 % confidence interval will be reported.

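### The 80% power assumes independent patients although ENVIE is delivered in therapy groups of 8–10; it holds only if the therapy-group correlation is close to zero

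*Protocol article*

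**What the plan says.** All references are to the protocol article.

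- **Sample size.** The inputs are a control rate ("For the control group the full remission rate at 15 months is expected to be 30" per cent), a difference ("If, in the experimental group, this rate is 15 % higher"), power 0.80 and two-sided 0.05. The result is that "with a power of 0.80 and a two-tailed significance level at 0.05, the sample size ends up to 166 patients per group", and "a total number of 332 subjects will be enrolled in the study". The section explains why there is no inflation for dropout. It gives no ICC, design effect or other allowance for group delivery, although it sets out the therapy groups in the same paragraph.
- **Add-on psychoeducational group program.** There are nine weekly "sessions led by two trained educators (nurse and medical doctor"), and "One or two psychoeducational groups of 8 to 10 patients will be planned in each center".
- **Eligibility assessment and randomization.** Individual patients are randomised from a "permuted-block 1:1 ratio randomization list with varying block sizes and will be stratified in participating centers".
- **Discussion.** The control condition is a waiting list, not a comparison group therapy.
- **Primary outcome.** "A Cox proportional hazard model will be used to assess the impact of the intervention (Effect size"), with methods for interval-censored data. Covariates may be added if the arms differ at baseline.
- **Secondary outcomes.** Response and relapse are to be analysed like the primary outcome, scores by a mixed model, and other comparisons by chi-square, Fisher, t or Mann–Whitney tests. No therapy-group effect is named anywhere.

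**The concern.** Patients are randomised individually, but those allocated to ENVIE are then treated together. A shared pair of educators, shared sessions and shared peers can make outcomes within a therapy group more alike than outcomes between groups. Controls have no such grouping, so the design is partially nested: clustered in one arm, singletons in the other.

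Any positive therapy-group correlation adds variance to the ENVIE remission rate that the independent-patient formula does not count. Two things follow. First, the power fixed by 332 patients is lower than the formula says. Second, an analysis that ignores the groups reports an interval that is too narrow and rejects a true null too often, unless something offsets this. Stratifying by centre does not remove the problem, because the therapy-group and educator component exists only under ENVIE. The covariate clause does not help either: therapy group is not a baseline characteristic on which the arms could be compared.

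The conclusion section would use a positive result to argue for wide dissemination, so the stated precision of the primary comparison matters.

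**Working it through.** **Inputs from the documents.** Control rate p1 = 0.30; ENVIE rate p2 = 0.45; mean rate 0.375; n = 166 per arm; two-sided α = 0.05; power 0.80; therapy-group size m = 8–10. The difference must be absolute: a relative 15% increase (34.5%) would need 1,693 per arm.

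**Assumption.** The documents give no ICC. I use g = 0.01, 0.05 and 0.10 for the therapy-group component beyond centre, with m = 9.

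**Step 1: reproduce the plan's figure.**
n = [1.960·√(2·0.375·0.625) + 0.842·√(0.30·0.70 + 0.45·0.55)]² / 0.15² = 162.3, so 163 per arm. The stated 166 is within 3% of this. Power at 166 is 80.9%. The figure therefore contains no clustering allowance and less than one point of slack.

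**Step 2: number of groups.** 166/10 = 16.6 and 166/8 = 20.8, so about 17–21 groups.

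**Step 3: variance inflation in the ENVIE arm only.** DE = 1 + (m − 1)·g, and

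power = Φ{[0.15 − 1.960·√(0.375·0.625·(1 + DE)/166)] / √[(0.21 + 0.2475·DE)/166]}.

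For g = 0.05: DE = 1 + 8·0.05 = 1.40. The standard errors are 0.0582 (null) and 0.0579 (alternative), so power = Φ[(0.15 − 1.960·0.0582)/0.0579] = Φ(0.62) = 73.2%. The effective ENVIE sample is 166/1.40 ≈ 119.

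**Step 4: interval width and type I error of an analysis that ignores groups.**
Width ratio = √[(0.21 + 0.2475·DE)/0.4575]. Type I error = 2·{1 − Φ[1.960/√((1 + DE)/2)]}, with no centre effect.

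| Assumed g | DE | Power at 166 per arm | Correct interval vs naive | Naive type I error |
|---|---|---|---|---|
| 0 | 1.00 | 80.9% | same | 5.0% |
| 0.01 | 1.08 | 79.3% | 2% wider | 5.5% |
| 0.05 | 1.40 | 73.2% | 10% wider | 7.4% |
| 0.10 | 1.80 | 66.5% | 20% wider | 9.8% |

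Over m = 8–10, power is 79.1–79.5% at g = 0.01 and 65.0–68.1% at g = 0.10.

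**Step 5: where 80% is lost.** Setting power to 0.80 gives DE = 1.044, so g = 0.044/(m − 1) = 0.0063, 0.0055 and 0.0049 for m = 8, 9 and 10.

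**Step 6: the centre offset.** Let c be the centre ICC, shared by both arms. With balanced arms within centre, c cancels from the between-arm difference, but an analysis without centre still counts it. True variance over naive variance is then [(1 − c + 8g) + (1 − c)]/2 = 1 − c + 4g. With c = 0.04 and g = 0.01 the ratio is 1.00 and there is no inflation. With c = g = 0.05 it is 1.15, and type I error is 2·{1 − Φ(1.960/√1.15)} = 6.8% rather than 7.4%. These c values are illustrative. The type I column above is therefore an upper figure for each g.

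**Step 7: check on the Cox scale.** HR = ln 0.55/ln 0.70 = 1.68, with 0.375·332 = 124.5 expected events. Schoenfeld's formula needs 118 events (82% power without clustering) and Freedman's needs 123. Applying the Step 6 ratio with c = 0, 124.5/117.7 = 1.058 = 1 + 4g gives g ≈ 0.014, and 124.5/123.0 = 1.012 gives g ≈ 0.003. The threshold moves with the formula but stays near zero.

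**The case against.** - **The ICC is unknown and may be small.** This stands. At 0.01 the loss is under two points of power and the interval barely changes. There are reasons to expect a modest value: remission is judged at 15 months, a year after the programme ends, by blinded raters, with usual treatment unrestricted. None of this shows the ICC to be negligible. A reader might infer that 80% power is certainly missed and the interval certainly too narrow; the documents do not support that, because both depend on an ICC they do not give.
- **The statistical analysis plan may handle it.** This stands for the analysis. A condensed article may leave frailty terms, random-effect structure and variance estimators to a plan not shown. Naming a Cox model without a group term does not prove that groups will be ignored, so the interval and type I figures describe a naive analysis, not an established one. It does not answer the power point: a later model can correct the interval but cannot restore power fixed by 332 patients.
- **Stratification by centre offsets the inflation.** Partly right, as Step 6 shows. The offset exists if centre effects are present and centre is left out of the model. It reduces the type I figures and can cancel them when g is small.
- **The power figures are approximate.** True: they use a difference in proportions rather than the planned Cox test. The Cox-scale check starts at 82% by Schoenfeld's formula and leads to a similar conclusion.

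**Conclusion.** The point holds in conditional form. The arithmetic behind 166 per arm is sound; the fault is its unstated assumption of no correlation within therapy groups. The stated 80% power holds only for a therapy-group ICC, net of centre, below about 0.005–0.006 on the two-proportion calculation.

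The cost ranges from trivial at an ICC of 0.01 to material at 0.05 or above. The documents give no basis for choosing within that range. The type I figures apply only if the analysis ignores therapy group, and they are upper values because they assume no centre effect. This should be fixed, but it does not by itself invalidate the design.

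**What to change.** 1. Record a therapy-group identifier for every ENVIE patient, most easily while the groups are being formed.
2. In the primary model and the mixed models, include the centre stratification factor and a therapy-group random effect in the ENVIE arm only, with controls as singletons. Alternatively, use a group-robust variance with a small-sample correction, since there are only about 17–21 groups.
3. Replace the claim of 80% power under independence with the power at 332 patients under an explicit assumed ICC, with its basis and a range. With groups of 9 this is about 73% at 0.05, and 79% to 66.5% over 0.01–0.10.

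The cost is one data item, some analysis wording, a slightly wider interval and a lower stated power. No extra patients are needed. If the sponsor preferred to keep 80% power, the partially nested calculation gives 169, 196 or 229 per arm at 0.01, 0.05 or 0.10. Applying the design effect to both arms would overstate the need (229 instead of 196 per arm at 0.05).

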**Fig. 1 Fig1:**
[figure not shown]
Study flow

Investigators should make every effort to minimize the number of patients lost to follow-up and obtain a maximum of information on patients lost to follow-up, particularly in looking for any adverse events.

To limit patients lost to the touch, participants in the intervention group will be sent a text message on their mobile phone (internet-based free site) one day before each psychoeducational session. Each participant will receive two text messages: one the week before and the other the day prior to each follow-up visit.

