This study will have some limitations. First, as in most longitudinal studies we will need to deal with the problem of missing values. Thus, since loss to follow-up will be considered as “not in remission”, positive results from this study will be particularly relevant. In order to limit patients lost to follow-up, participants in the intervention group will be sent a text message on their mobile phone one day before each psychoeducational session, and one week and one day before each follow-up visit. Second, patients will be randomized, but there is no double-blind, randomization since the patient will know if he/she belongs to the intervention or control group. Indeed, the control group will consist of a waiting list, and not a control group therapy. Third, we will not have any control over the treatment as usual in each of the two groups.

There will also be several strengths to this study, including the strong methodology of a randomized controlled design, validated assessments conducted by independent raters blinded to treatment condition, a sample defined by a standard diagnostic measure, an appropriate statistical analysis plan, and considering patients lost to follow-up as not in remission. Furthermore, the long-term follow-up (15 months), the assessment of remission and treatment adherence, and the latest innovative scientific didactic content of this short-duration program are highly relevant in these studies. Given these strengths, the results of the study should further enhance the evidence-based data supporting psychoeducational intervention for MDD. Finally, given the 11 French investigator centers implied in this study, the results could be easily generalized to depressed patients visiting French medical centers.

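### Counting lost patients as not in remission does not by itself remove the need for a dropout allowance, and it is conservative only if loss is no higher in the waiting-list arm

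*Protocol article*

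**What the plan says.** The Sample size section sets the control rate: "For the control group the full remission rate at 15 months is expected to be 30" per cent. The assumed benefit is put as "If, in the experimental group, this rate is 15 % higher". The error rates are fixed in the words "with a power of 0.80 and a two-tailed significance level at 0.05", and the section concludes that "the sample size ends up to 166 patients per group". Because losses are to be counted as not in remission, it then states that "no adjusted sample size for taking dropouts into account has to be established". The Primary outcome section repeats the failure rule. No expected loss rate is given anywhere.

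The Discussion names missing values as the first limitation, answers it with the same rule, and infers that "positive results from this study will be particularly relevant". It later lists the rule among the strengths of the study.

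Visit reminders are described twice. The text under Fig. 1, in the Assessments section, limits the session reminders to the intervention group but says of the visit reminders: "Each participant will receive two text messages: one the week before and the other the day prior to each follow-up visit". The Discussion puts both kinds into one sentence with one subject: "participants in the intervention group will be sent a text message on their mobile phone one day before each psychoeducational session, and one week". The rest of that sentence covers the visit reminders, still with the intervention group as its subject.

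**The concern.** Two separate claims are drawn from one rule. The first is that it makes a dropout allowance unnecessary. Counting a lost patient as a failure does preserve the number analysed, but power also depends on the size of the difference. If some lost patients would have remitted, recoding them lowers both rates and brings them closer together.

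The second claim is that the rule makes a positive result more convincing. That depends on which arm loses more patients. Every lost patient becomes a failure, so the rule penalises the arm with more loss. Patients know their allocation and controls are on a waiting list, while ENVIE patients attend nine sessions with a text before each one. Better retention under ENVIE is therefore plausible, though not established. If it occurred, part of an apparent remission benefit would be a retention difference.

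At stake are the 80% power on which the sample size rests and the reading of a positive primary result.

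**Working it through.** **Inputs from the Sample size section.** Control 30%; ENVIE 45% (the 15% read as absolute points, since a relative 15% would need about 1,693 per arm); two-sided 5% level; power 0.80; n = 166 per arm.

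**Assumed inputs.** Loss rates, because the article gives none.

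**Method.** Two-proportion normal approximation with p̄ = (p1 + p2)/2, Δ = p2 − p1, SE0 = √[2p̄(1 − p̄)/n], SE1 = √{[p1(1 − p1) + p2(1 − p2)]/n}, and power = Φ[(Δ − 1.96·SE0)/SE1].

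**Step 1: the plan's own figure.** Solving for 80% power at 30% against 45% gives 162.3, so 163 per arm, close to the stated 166. At n = 166, SE0 = 0.0531 and SE1 = 0.0525, so power = Φ[(0.15 − 0.1042)/0.0525] = Φ(0.873) = 80.9%. The sample size reproduces, with little to spare.

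**Step 2: equal loss d in both arms.** Suppose 30% and 45% are rates among followed patients and loss is unrelated to remission. The rates under the failure rule are 0.30(1 − d) and 0.45(1 − d), and the difference is 15(1 − d) points.

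| Assumed loss | Control | ENVIE | Difference (points) | Power at 166 per arm |
|---|---|---|---|---|
| 0% | 30.0% | 45.0% | 15.0 | 80.9% |
| 1% | 29.7% | 44.55% | 14.85 | 80.2% |
| 5% | 28.5% | 42.75% | 14.25 | 77.6% |
| 10% | 27.0% | 40.5% | 13.5 | 74.1% |
| 20% | 24.0% | 36.0% | 12.0 | 66.6% |

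For example, at 10%: SE0 = 0.0519, SE1 = 0.0514, and Φ[(0.135 − 0.1017)/0.0514] = Φ(0.648) = 74.1%.

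**Step 3: loss related to remission.** Take 30% and 45% as the rates under complete follow-up, and let lost patients remit half as often as their arm as a whole. At 20% loss, both rates are multiplied by 1 − 0.20 × 0.5 = 0.90. That is the 10% row above, so power is 74.1% and not 66.6%. If no lost patient would have remitted, the multiplier is 1 and power does not fall.

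**Step 4: unequal loss with no true effect.** Both arms have the same true remission rate p, and loss is unrelated to remission. Assumed loss is 10% under ENVIE and 15%, 20% or 25% in controls. The observed rates are 0.90p and p(1 − control loss). The rejection rate is the sum of both tails of the same test.

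| True p | Control loss | ENVIE observed | Control observed | Spurious difference (points) | Two-sided rejection |
|---|---|---|---|---|---|
| 30% | 15% | 27.0% | 25.5% | 1.5 | 6.1% |
| 30% | 20% | 27.0% | 24.0% | 3.0 | 9.6% |
| 30% | 25% | 27.0% | 22.5% | 4.5 | 15.8% |
| 45% | 15% | 40.5% | 38.25% | 2.25 | 7.0% |
| 45% | 20% | 40.5% | 36.0% | 4.5 | 13.4% |
| 45% | 25% | 40.5% | 33.75% | 6.75 | 24.6% |

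The nominal level is 5%. The reverse pattern biases against ENVIE: at p = 30%, with 20% loss under ENVIE and 10% in controls, the difference is −3.0 points.

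**Step 5: the reminder passages.** The Assessments text separates session texts (intervention group) from visit texts (every participant). The Discussion sentence, read grammatically, gives both to the intervention group. They cannot both be right about visit texts.

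**The case against.** The strongest reply is that the 30% and 45% may already be rates of the outcome as analysed, with losses counted as failures. The failure rule stands in the same paragraph as the 30%. On that reading no allowance is needed and power stays at 80.9%. This stands as a possibility: the article does not say which reading applies, and the source cited for the 30% is not at hand. But the article does not give this as its reason. It rests the absence of an allowance on the failure rule alone.

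A reader might infer that power falls below 80% with any loss at all. The figures do not support that: at 1% loss it is 80.2%, and the fall is smaller or absent if lost patients would have remitted less often.

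A reader might also infer that only ENVIE patients receive visit reminders, so that unequal retention is built into the design. The documents do not support that either. The Methods text gives visit reminders to each participant, and the contrary statement is one merged sentence in the Discussion. What remains is a wording conflict.

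The Completer Set analysis in General statistical considerations is a partial safeguard, because it does not count losses as failures. However, it only drops patients without a valid 15-month measurement. It does not show how different the lost patients would have to be, in each arm, to change the conclusion.

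Finally, the planned primary analysis is a Cox model for interval-censored data, not a two-proportion test. The figures here use the two-proportion test because it reproduces the sample size; they describe the planning calculation and only approximate the behaviour of the final model.

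**Conclusion.** The point holds in a conditional form. The stated reason for making no dropout allowance is not sufficient, and the calculation is sound only if 30% and 45% are already net of loss. If they are rates among followed patients, with equal loss unrelated to remission, the stated 80% is not met once loss reaches a few per cent, and the shortfall is material at 10% to 20% loss. The size rests on assumed loss rates.

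The Discussion's claim that the rule strengthens a positive result is wrong as a general statement. It holds only if loss is not higher in the waiting-list arm. Under the assumed patterns of higher control loss, the false-positive rate rises from slightly above nominal to roughly three times nominal at 30% remission, or five times at 45%. The direction and size of any actual imbalance are unknown. The reminder passages conflict and need reconciling, but unequal visit reminders are not established.

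**What to change.** 1. In the Sample size section, state that 30% and 45% are net of loss, if that is so. Otherwise replace the no-adjustment sentence with the power at a stated expected loss and the assumption behind it.
2. In the Discussion, withdraw the claim that the failure rule gives positive results extra weight, and its listing as a strength. Say instead that its direction depends on loss by arm.
3. Align the Discussion's reminder sentence with the Assessments text, so that visit reminders are described as the same in both arms.
4. Add a sensitivity analysis of the primary outcome that varies the assumed outcome of lost patients separately by arm, for example a tipping-point analysis, alongside the Completer Set.

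The cost is wording, one extra analysis and possibly a less favourable stated power. No more patients are required.
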